# Implementing evidence-based recommended practices for the management of patients with mild traumatic brain injuries in Australian emergency care departments: study protocol for a cluster randomised controlled trial

**DOI:** 10.1186/1745-6215-15-281

**Published:** 2014-07-11

**Keywords:** Mild traumatic brain injury, Cluster trial, Emergency department

## Abstract

**Background:**

Mild head injuries commonly present to emergency departments. The challenges facing clinicians in emergency departments include identifying which patients have traumatic brain injury, and which patients can safely be sent home. Traumatic brain injuries may exist with subtle symptoms or signs, but can still lead to adverse outcomes. Despite the existence of several high quality clinical practice guidelines, internationally and in Australia, research shows inconsistent implementation of these recommendations. The aim of this trial is to test the effectiveness of a targeted, theory- and evidence-informed implementation intervention to increase the uptake of three key clinical recommendations regarding the emergency department management of adult patients (18 years of age or older) who present following mild head injuries (concussion), compared with passive dissemination of these recommendations. The primary objective is to establish whether the intervention is effective in increasing the percentage of patients for which appropriate post-traumatic amnesia screening is performed.

**Methods/design:**

The design of this study is a cluster randomised trial. We aim to include 34 Australian 24-hour emergency departments, which will be randomised to an intervention or control group. Control group departments will receive a copy of the most recent Australian evidence-based clinical practice guideline on the acute management of patients with mild head injuries. The intervention group will receive an implementation intervention based on an analysis of influencing factors, which include local stakeholder meetings, identification of nursing and medical opinion leaders in each site, a train-the-trainer day and standardised education and interactive workshops delivered by the opinion leaders during a 3 month period of time. Clinical practice outcomes will be collected retrospectively from medical records by independent chart auditors over the 2 month period following intervention delivery (patient level outcomes). In consenting hospitals, eligible patients will be recruited for a follow-up telephone interview conducted by trained researchers. A cost-effectiveness analysis and process evaluation using mixed-methods will be conducted. Sample size calculations are based on including 30 patients on average per department. Outcome assessors will be blinded to group allocation.

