### Blinding

Due to the nature of the intervention, it will not be possible to blind ED staff members to group allocation. To limit the possibility of selection and detection bias, chart auditors will be independent, where possible, of the hospital. In instances where the hospital does not approve an independent chart auditor, a solution will be discussed which aims to reduce the risk of selectively identifying patients (for example, using a staff member from another unit who will receive training from the research team). External chart auditors and the trial statistician will be blinded to group allocation.

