#### Secondary outcomes

##### Clinical practice outcomes

Two other measures for PTA were selected as secondary outcomes. ‘PTA screening-tool’ measures whether the administration of the validated tool was completed at least once. ‘Memory-clinical’ measures whether staff members have made an assessment of memory using questions in their clinical assessment. Other secondary measures assessing the effectiveness of the intervention in improving the ED management of mTBI are listed in Table 3. On the cohort of patients for whom risk criteria are recorded, ‘CT scan-clinical criteria’ (CT) measures whether a CT scan was provided in the presence of a risk factor that justifies the scan (see Additional file 1). This measure is therefore indicating whether a scan was appropriately received; however, we will not be able to measure whether a scan was ‘appropriately denied’ because of the inconsistency in recorded clinical criteria. ‘Provision of patient information’ (INFO) measures whether information was recorded as provided upon discharge home from the ED. Via the chart audit, we will not be able to measure what information was handed out (for example, the information used in our intervention [40] or other). However, this will be assessed in the patient follow-up interview in NET-Plus hospitals. Two measures of ‘safe discharge’ are included, the first being a composite score of PTA and INFO (for all patients), and the second provides a composite measure of whether the patient received appropriate care for all of the three clinical practices (PTA, CT, INFO; for the subgroup of people for whom risk criteria were recorded).

Clinical practice outcomes will be measured retrospectively through chart audit by an independent, trained chart auditor. Data will be collected over the 2 month period following the last intervention component.

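### The abstract's unqualified claim of blinded outcome assessors is not secured for hospital-based chart auditors, and the body of the article does not address it for NET-Plus interviewers

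*Protocol article*

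**What the plan says.** The abstract (Methods/design) introduces two kinds of outcome collector, independent chart auditors and trained telephone researchers, and then states: "Outcome assessors will be blinded to group allocation". Under Clinical practice outcomes the auditor is again described as independent, without exception.

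The Blinding section sets out the conditions. It accepts that "it will not be possible to blind ED staff members to group allocation". On auditors it says that "chart auditors will be independent, where possible, of the hospital". It then adds: "In instances where the hospital does not approve an independent chart auditor, a solution will be discussed". The example given is "using a staff member from another unit who will receive training from the research team", and the stated purpose is that the solution "aims to reduce the risk of selectively identifying patients". The closing sentence on who is blinded reads: "External chart auditors and the trial statistician will be blinded to group allocation".

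Under Ethical review and informed consent (Patients, NET component), the auditor confirms eligibility and collects the outcome data at the same time.

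Under Patient and cost outcomes, trained researchers collect the NET-Plus outcomes by computer-assisted telephone interview. Table 5 stars anxiety as the primary outcome among these. The chart cannot show which leaflet or booklet a patient was given. On that, the Clinical practice outcomes section says: "However, this will be assessed in the patient follow-up interview in NET-Plus hospitals". Table 2 lists the study booklet among the materials for the intervention group only.

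**The concern.** Readers use a blinding statement to judge the risk of detection bias. Here the headline statement is wider than the procedure behind it.

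The primary outcome comes from the chart audit. An in-house auditor who knows the arm could affect it in two ways: by which patients are counted as eligible, and by whether screening is judged to have met the definition. One person makes both decisions, so numerator and denominator are exposed together.

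The NET-Plus outcomes are subjective and collected by telephone, so an interviewer who learns the arm could prompt or record differently. The article expects patient information to reduce anxiety and symptoms, and those scales are collected in the same call as the question on information received.

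**Working it through.** The plan gives no figure on this point, so the check sets the statements side by side.

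| Role | What the role assesses | Abstract | Blinding section |
|---|---|---|---|
| External chart auditor | Eligibility, primary and other chart outcomes | Blinded | Blinded |
| In-house auditor from another unit | The same | Blinded, by the general wording | Not stated |
| NET-Plus interviewer | Anxiety, symptoms, activities, SF-12, healthcare use | Blinded, by the general wording | Not mentioned |
| Trial statistician | No outcome assessment | Not mentioned | Blinded |

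**In-house auditors.** The Blinding section describes the fallback auditor and then restricts its promise to external auditors. The stated aim of the fallback concerns selection of patients, not blinding of extraction. So the article provides for a group of assessors of the primary outcome to whom the abstract's statement is not shown to apply.

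**How much data this could involve.** The sample size section gives 30 EDs, 15 per group, averaging 30 patients, 900 in total.
- Share of one ED: 30/900 = 1/30 = 3.3%. This is an average, because cluster sizes vary (assumed coefficient of variation 0.47).
- The number k of EDs with an in-house auditor is not given. Taking k = 1, 3 and 6 purely as assumptions, the share k/30 is 3.3%, 10% and 20% (30, 90 and 180 patients).
- If all k fell in one group, the share of that group, k/15, would be 6.7%, 20% and 40%. An error of d percentage points in those EDs would move the group's crude rate by (k/15) × d. For k = 3 that is one fifth of d.

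These figures show how much data is exposed. They do not estimate a bias, because neither k nor d can be obtained from the document.

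**Interviewers.** Table 5 lists 7 anxiety, 13 symptom, 2 activity and 12 quality-of-life items: 7 + 13 + 2 + 12 = 34. It also lists 1 re-presentation, 3 healthcare-visit and 4 medication items: 1 + 3 + 4 = 8, giving 42 by interview. The count describes what the interviewer handles, not how much of it would be distorted. The article does not state interviewers' access to allocation or the order of the questions.

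**The case against.** The case against has real weight.

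- **The fallback is disclosed and limited.** It applies only where a hospital refuses an external auditor, possibly nowhere. The example is someone from outside the ED, and the people the article says cannot be blinded are ED staff. Such a person might not know the arm.
- **Auditor discretion is constrained.** The Primary outcome section relies on an objective score in the record. The Data quality assurance section requires auditors to work through the same pilot records until consistent, with a manual and data-entry checks. The section on identifying study patients adds an identification protocol and a record of the process used in each hospital.
- **Interviewers.** A reader might infer that they are unblinded, or that the Blinding section contradicts the abstract about them. Neither follows. The abstract's sentence can be read as covering them, the Blinding section does not mention them, and an article may leave interview procedures to a fuller document.
- **Question order.** A reader might also infer that the information item unmasks the interviewer before the scales are completed. The order is not given, the item relies on recall at 3 to 5 months, and the patient may have received other information. It is a possible clue, no more.
- **Sensitivity analyses** may be in the analysis plan, which is not shown. Their absence is not a fault here.

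These points limit the likely size of any bias and reduce the interviewer part to a safeguard. They do not reconcile the abstract's unqualified sentence with a Blinding section that allows non-external auditors and leaves them out of its promise.

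**Conclusion.** The concern holds for chart auditors. As written, the claim of blinded outcome assessment is secured for external auditors but not for any in-house auditor, who would handle both eligibility and the primary outcome. The exposed share is k/30 of the primary-outcome data on average, with k unknown and possibly zero. Bias is probably modest, given the objective score, the auditor training and the identification protocol. That judgement assumes these measures work as described and that an in-house auditor outside the ED has little stake in the result.

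For NET-Plus interviewers the finding is narrower. Beyond the abstract's general promise the article does not address their blinding, and one interview item may hint at the arm. The document does not support saying that they know the allocation or that the 34 clinical and quality-of-life items are biased.

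The point should still be settled, because it determines whether the trial can report blinded assessment without qualification.

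**What to change.** 1. Reconcile the abstract, the Blinding section and the Clinical practice outcomes section. State blinding status separately for external auditors, in-house auditors and interviewers, and claim it only where it is secured.
2. Record for each ED whether the auditor was external or in-house. The letter of understanding, signed before randomisation, already covers the process for authorising the auditor, so it is a natural place to settle this before allocation is known.
3. Repeat the primary analysis in EDs with an external auditor only, as a sensitivity analysis. It will be less precise because it uses fewer clusters, and should be read for consistency with the main result.
4. As a safeguard, keep ED allocation from the interviewers, and ask which information was received only after the anxiety, symptom, activity and SF-12 items are complete. The database already assigns access by role and the interview is computer-assisted, so both steps are easy to set up.

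The cost is one extra field, one sensitivity analysis, an access and script setting, and a less favourable blinding statement.

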**Trial registration:**

Australian New Zealand Clinical Trials Registry ACTRN12612001286831 (date registered 12 December 2012).

## Background

Head injuries are a frequent presentation to emergency departments (EDs) worldwide. They are caused by external forces to the head (such as sport, falls, motor vehicle accidents, assaults or blast injuries) [1]. Country-based incident estimates range from 108 to 332 hospitalised new cases per 100,000 population per year [2], and the incidence is rising as a consequence of increased transport-related injuries in low- and middle-income countries [1]. Traditionally, head injuries are classified as mild, moderate or severe head injury, depending on the patient’s presenting level of consciousness as expressed by the Glasgow Coma Scale (GCS) score [3]. The scale ranges from a low of 3 (comatose) to 15 (awake and following commands). The vast majority of patients (80 to 90% depending on definitions) present with normal or near normal GCS scores (14-15/15) and are therefore classified as “mild”. In non-paediatric patients, the highest incidence of mild traumatic brain injury (mTBI) is seen in males between the ages of 15 and 24 years and in men and women 65 years of age and older [4].

In most cases, patients who experience mTBI will recover fully, typically within days to months. Up to 15% of patients with a normal GCS score of 15 have an acute lesion on head computed tomography (CT), but less than 1% of these patients have a lesion that requires neurosurgical intervention [4-6]. However, up to 15% of patients diagnosed with mTBI experience persistent disabling problems [7,8] including reduced functional ability, heightened emotional distress, and delayed return to work or school [9,10] 3 months or more after injury. As the ED is the main, and often only, point of medical contact for these patients, ED care may provide opportunities to impact on the outcomes of these patients.

The challenge for the emergency physician is to identify which patients with a head injury have an actual traumatic brain injury (TBI) requiring further management, and which patients can safely be sent home [4]. Patients with subtle symptoms or signs can still progress to suboptimal outcomes [4]. Despite the existence of several high quality evidence-based clinical practice guidelines (EBCPGs) internationally and in Australia [11], research shows inconsistent implementation of recommended practices. In earlier phases of our study, relevant EBCPGs were identified and assessed for their quality [11]. Subsequently, key clinical recommendations and the evidence underpinning these recommendations were studied, and two consensus meetings were organised to develop locally relevant recommendations to serve as the basis for developing our management outcome measures [12]. Table 1 outlines the evidence-based recommendations, their relevance to the management of this patient group, and evidence regarding gaps in practice.

**Table 1 T1:** Key clinical recommendations in the management of mild traumatic brain injury in emergency departments

**Key recommendations and relevance to management**	**Research highlighting the ‘evidence-practice’ gap**
**Post-traumatic amnesia should be prospectively assessed in the emergency department using a validated tool**	
Post-traumatic amnesia (PTA) is defined as "an interval during which the patient is confused, amnestic for ongoing events and likely to evidence behavioural disturbance" [13]. It may manifest as repetitive questioning or short-term memory deficits [14] and has been shown to have better predictive ability with clinical outcomes compared with Glasgow Coma Scale (GCS) [15-18] (GCS assesses consciousness but not whether the patient is able to lay down new memories). Various validated tools to asses PTA are available such as the Revised Westmead PTA tool, or the Abbreviated Westmead PTA scale (A-WPTAS), the latter being an extended version of the GCS and specifically developed for use in the emergency department (ED). The A-WPTAS standardises some of the questions of the GCS and adds a memory test. Screening for PTA using such a validated tool may reduce the risk of failing to classify mild traumatic brain injury (mTBI) patients and prevents patients from being discharged from hospital while they are suffering from acute cognitive impairment [19,20].	A retrospective audit in two Australian EDs showed rates of assessment of PTA in adults (for those with an initial GCS of 14 or 15) as 0% (95% CI 0% to 14%; n = 24) in one hospital, and 31% (95% CI 24% to 39%; n = 164) for a second (which had a protocol in place) ([name], [name], unpublished observations). We are not aware of any published studies reporting rates in adults.
**Guideline-developed criteria or clinical decision rules should be used to determine the appropriate use and timing of computed tomography imaging**	
The aims of using clinical decision rules to determine the need for a computed tomography (CT) scan are to ensure patients at risk of developing intracranial injuries receive a scan, and to decrease unnecessary scanning. Several clinical decision rules have been developed worldwide, some of which have been externally validated, most notably the Canadian Computed Tomography Head Rule (CCTHR) [21] and the New Orleans Criteria [22]. However, both these rules used loss of consciousness or amnesia as entry criteria, which means they could not be reliably used for all patients presenting to the ED with a head injury. Studies show that intracranial complications can also occur without loss of consciousness/PTA, particularly in the presence of other risk factors [23-25]. Therefore, more recent guidance has been developed that is applicable to all patients irrespective of presence or absence of loss of consciousness/PTA [4,14,26]. Most evidence-based clinical practice guidelines for the management of patients with mTBI have adapted one or more of these rules. They show considerable concordance [27]. The Institute for Trauma and Injury Management, New South Wales, developed simple recommendations for the identification of high risk patients based on the presence of single criteria that are applicable in the Australian setting [14].	It is difficult to establish target rates for appropriate CT scanning in patients with mTBI (that is, the percentage of mTBI patients who should receive a scan) because this is dependent on the case mix of patients (for example, hospitals that service an older demographic may (appropriately) have higher CT scanning rates for mTBI patients) and the leniency of the rules or guidelines. A study comparing percentages of scans that would be required by applying six different rules found rates between 50% and 71% [28]. A Canadian study using the CCTHR estimated a rate as low as 62.4% was possible and safe [29]. Estimates of how frequently appropriate decisions are made about the need for CT scanning (in populations with slightly variable definitions and using several different rules) range from 66% in the UK [30], 73% in Scandinavia [31], 82.5% in Canada [29], 80% and 92% in indigenous and non-indigenous Australians [32], and 65% to 91% in the US [33]. A study [34] surveying Australian ED physicians (response rate 54.2%, n = 417) showed that 82% had awareness of CCTHR but only 32% used it.
**Verbal and written patient information consisting of advice, education and reassurance should be provided upon discharge from the emergency department**	
Providing patients with information upon discharge serves two purposes: 1) to inform the family/carer about what to observe and what actions to take if the patient’s neurologic condition deteriorates significantly after discharge from the ED [35]; and 2) to provide information regarding post-concussive symptoms, symptom management, and prevention of future head injuries [36-39]. A randomised controlled trial [40] of 202 adults with mTBI in Australia evaluated the impact of patient information (booklet) on outcomes. The booklet outlined common symptoms associated with mTBI, their likely time course and suggested coping strategies. By 3 months, the intervention group had lower scores on most items on a post-concussion checklist, significantly so for anxiety (*P* < 0.04) and sleeping difficulty (*P* < 0.01). They also had lower scores on a ‘global severity’ score. There was no statistical difference between the groups on formal neuropsychological assessment.	Studies show that a large proportion of mTBI patients do not receive written information upon discharge from the ED, ranging from 36% [41] and 51% [30] in the UK, to 63% in the US [42]. Studies looking at the quality and content of discharge pamphlets [35,37,38,43] found that the information regarding post-concussive symptoms and reassurance is missing in 41% [37] to 60% [38] of pamphlets reviewed. One study surveyed nurses (25% response rate) regarding their teaching habits [36], and concluded that in general they were more focused on providing injury-specific information and less on mTBI, symptom management or strategies to prevent future brain damage.

We are not aware of trials which have evaluated implementation of this suite of recommendations in ED practice internationally or in Australia. A cluster randomised trial (CRT) performed by Stiell and colleagues [29] in Canada implemented the Canadian CT Head Rule (CCTHR) to reduce unnecessary CT scans. Their implementation intervention package included education (distribution of articles describing the development and validation of the rule, pocket cards and posters, and a 1-hour teaching session to review the evidence and clinical application of the rule), and a mandatory real-time reminder of the rule at the point of CT scan request that required checking off the rule before the scan would be performed by the imaging department [29]. The intervention was designed to be low-cost and simple and had been shown to be effective in reducing cervical spine imaging rates for neck trauma in a simultaneous study [44]. In the implementation of the CCTHR, the intervention failed to reduce the number of CT scans requested; in fact, CT imaging rates increased in both intervention and control group (62.8% before compared with 76.2% after, absolute difference +13.3%, and 67.5% to 74.1%, absolute difference +6.7%, respectively; a difference in change between groups of 6.6%). However, the baseline rates were much lower than expected and approaching the estimated ‘safe’ rate (62.4%), which may have reduced the likelihood of further reductions (that is, indication of a ceiling effect) [29].

Increasingly it is considered best practice to base interventions aiming to change clinical practice on a theoretical approach to identifying factors potentially influencing practice change [45]. Theory can offer a generalisable framework for considering effectiveness across different clinical conditions and settings [46], and, given the wide variety of factors that may influence practice change, basing interventions on different theoretical assumptions may prevent overlooking important factors [47] and will ultimately help to understand how and why change is achieved. Additionally, this approach offers the possibility of optimising interventions to increase effect sizes in subsequent studies.

